## Abstract

Closed reduction is a common treatment method for developmental dysplasia of the hip (DDH) in children aged 6–18 months. Residual acetabular dysplasia (RAD) is the most common complication associated with closed reduction. Residual limbus inversion (RLI) is a common condition following DDH closed reduction. Previously, we confirmed that when limbus inversion exceeds 32.2% of the acetabular depth after closed reduction, RLI persists and leads to RAD; however, this was based on a small cohort with a short-term follow-up period. The long-term fate of RLI and the correlation between RLI and RAD have yet to be verified. Therefore, this multicenter clinical study protocol was designed in three parts to investigate the effect of RLI on acetabular development after closed reduction of DDH (a multicenter retrospective cohort study), effect of RLI clearance on acetabular development (a multicenter retrospective and prospective randomized controlled study), and influence of inverted limbus clearance on acetabular development during DDH reduction (a multicenter prospective cohort study). Statistical analysis was performed by assessing the basic measures of acetabular development including the acetabular index and central-edge angle using frontal pelvic radiographs; the magnitude of limbus inversion, cartilaginous acetabular index, and T1ρ mapping values were measured using magnetic resonance imaging. The multicenter retrospective cohort studies required 5 years of follow-up period at minimum, and the prospective randomized controlled studies required reviews of frontal pelvic radiographs every 6 months as well as data pooling every 2 years to compare the short- and mid-term outcomes of hip joint morphological development between the two groups of pediatric patients. This research program is expected to verify that RLI following closed reduction of DDH can affect acetabular development and that limbus excision during DDH reduction can improve postoperative RAD. Therefore, the indication and timing of surgical intervention for RLI after closed reduction of DDH provide a basis for revising the acceptable criteria for utilizing closed reduction of DDH to reduce the incidence of osteoarthritis caused by RAD following DDH treatment.

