##### Statistical analysis

2.2.1.4.

Statistical analysis was performed using SPSS 27.0 software (IBM, SPSS Inc.).
1.To ensure consistency and reliability between multicenter research samples, it is first necessary to conduct a consistency analysis on the structural data, such as age and sex, of the included cases from each center and the International Hip Dysplasia Institute (IHDI) classification using the Cohen's kappa statistic. Simultaneously, the baseline characteristics (such as structural composition and pathological severity) of the included cohorts within each center must be consistent; imbalances in baseline characteristics were corrected by increasing the sample size.2.The included patients were divided into the non-limbus inversion group (A) and the limbus inversion group based on the presence of limbus inversion at closed reduction. The limbus inversion group was then further divided into the RLI group (B) and the resolved inverted limbus group (C) according to the state at final follow-up. A combination consisting of any two of the groups was organized into cohorts. Fisher's precision probability test was used to compare the difference between the sexes and affected sides, using analysis of variance to compare the different ages between the two groups. Differences in acetabular index was compared using Student's *t*-test. Chi-square test was used to compare IHDI classification, VAS and HHS, and Severin classification at the final follow-up, and analysis of variance was used to compare the MRI T1ρ mapping values and the difference in the initial magnitude of limbus inversion between groups B and C, as well as the difference between the initial magnitude of limbus inversion and that at the final follow-up in group B.3.ROC curve analysis was used to predict the cut-off value of the initial magnitude of limbus inversion in the case of persistent RLI as well as calculate its specificity, sensitivity, and statistical significance.4.Sample size calculation.In this study, ossification of the acetabular cartilage was the main observation; thus, improvement of the acetabular index was the most suitable observation indicator. The sample size calculation was based on the previously published acetabular index at the final follow-up in the group with RLI and the group without RLI after closed reduction (21.41°±3.61° and 18.88 ° ± 4.32° in the two groups, respectively) (15). The significance level *α*, the statistical power of the test, the ratio of the sample sizes in the two groups, and the percentage of patients lost to follow-up were set at 0.05, 0.9, 1:1, and 20%, respectively. The minimum sample size for each group was calculated to be 67 cases (134 cases in total). Therefore, at least 67 cases needed to be enrolled in the observation group and the control group, respectively.

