###### Inclusion criteria

2.2.2.1.1.

Inclusion criteria 1–5 are the same as the previously listed inclusion criteria 1–5 (2.2.1.1);

6. More than 1 year after closed reduction;7. Patients aged ≤5 years at follow-up;8. The magnitude of limbus inversion exceeded 32% of the horizontal depth of acetabular roof at follow-up (or the cut-off value obtained in Protocol 2.2.1);9. The acetabular index was ≤30° at follow-up (since an acetabular index>30° usually necessitates pelvic osteotomy).

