##### Cohort grouping and interventions

2.2.3.2.

For cases meeting the assessment criteria specified in 2.3.1, the labral morphology was further evaluated using intraoperative arthrograms if there was no limbus inversion or if magnitude of the limbus inversion was <32% of the horizontal depth of the acetabular roof (or the cut-off value obtained in 2.2.1). A closed reduction using Spica cast immobilization was then performed to construct the control cohort. If intraoperative evaluation suggested that the magnitude of limbus inversion exceeded the cut-off, open reduction with post-reduction Spica cast immobilization was performed, in which the acetabular soft tissues were removed *via* the bikini incision approach, and the inverted limbus was excised. Patients undergoing open reduction procedures constituted the experimental cohort. Patients in the two cohorts underwent post-reduction cast immobilization for 3 months followed by immobilization with braces for 3 months.

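### Part 1 derives the limbus-inversion cut-off and scores its accuracy on the same children, so the reported sensitivity and specificity will on average be somewhat too high

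*Protocol article*

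**What the plan says.** Section 2.2.1.4, item 2, splits the children with limbus inversion at reduction into two classes: they are "further divided into the RLI group (B) and the resolved inverted limbus group (C) according to the state at final follow-up". Item 3 then reads: "ROC curve analysis was used to predict the cut-off value of the initial magnitude of limbus inversion in the case of persistent RLI", and continues "as well as calculate its specificity, sensitivity, and statistical significance". Derivation and scoring are one step on one cohort. The article names no hold-out sample, resampling correction or separate validation set. It also does not say how the cut-off is picked from the curve or how large groups B and C will be.

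The result is carried forward twice. In part 2 (section 2.2.2.1.1, criterion 8) a child is eligible if inversion at follow-up exceeds 32%, "or the cut-off value obtained in Protocol 2.2.1". In part 3 (section 2.2.3.2) the same alternative appears, "or the cut-off value obtained in 2.2.1", and there it allocates treatment: "If intraoperative evaluation suggested that the magnitude of limbus inversion exceeded the cut-off, open reduction with post-reduction Spica cast immobilization was performed".

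A cut-off already exists. The Abstract reports that "when limbus inversion exceeds 32.2% of the acetabular depth after closed reduction, RLI persists and leads to RAD", and adds that this came from a small cohort with short follow-up.

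**The concern.** A cut-off chosen because it performs well in a sample fits that sample's noise as well as its signal. Its sensitivity and specificity in that sample are therefore higher, on average, than they would be in new children. This matters here because the cut-off is a main product of part 1. It may set eligibility in part 2 and allocation in part 3, and the programme aims to inform revised criteria for an acceptable closed reduction. Readers will judge the cut-off by the accuracy reported for it.

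There is also an opportunity that the article does not mention. Because 32.2% was fixed beforehand in other data, scoring it in the new multicentre cohort would give accuracy free of this selection effect, as long as children from the earlier cohort are left out.

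**Working it through.** **1. The plan's own figure.** The only sample size in the article is for acetabular index, not for the ROC analysis. Inputs from section 2.2.1.4, item 4: "21.41°±3.61° and 18.88 ° ± 4.32° in the two groups, respectively", α 0.05, power 0.90, ratio 1:1, loss 20%.

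- Difference: 21.41 − 18.88 = 2.53.
- Pooled variance: (3.61² + 4.32²)/2 = (13.03 + 18.66)/2 = 15.85, so SD = 3.98.
- n = 2 × 15.85 × (1.960 + 1.282)² / 2.53² = 52.03, rounded up to 53 per group (two-sided).
- With 20% loss: 53/0.80 = 66.25, rounded up to 67.

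The stated 67 per group is reproduced. It says nothing direct about the size of groups B and C, which are the two ROC classes.

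**2. Size of the optimism.** The article gives no AUC, sensitivity or specificity, so the effect was simulated. Assumptions: inversion is normal with SD 1 in both classes, means differ by √2·Φ⁻¹(AUC), and the cut-off maximises sensitivity + specificity − 1 (Youden's J). Apparent accuracy is that of the chosen cut-off in its own sample. True accuracy is that of the same cut-off in the population. There were at least 3,000 samples per setting. Figures are percentages, with differences taken before rounding.

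| AUC | Hips per class | Apparent sens / spec | True sens / spec | Overstatement (sens, spec) |
|---|---|---|---|---|
| 0.7 | 67 | 69.6 / 65.4 | 65.5 / 61.6 | 4.0, 3.8 |
| 0.8 | 67 | 76.5 / 73.5 | 73.0 / 70.2 | 3.5, 3.4 |
| 0.9 | 67 | 84.7 / 82.9 | 81.9 / 80.0 | 2.7, 2.8 |
| 0.7 | 34 | 71.2 / 66.8 | 65.6 / 61.0 | 5.7, 5.8 |
| 0.8 | 34 | 78.4 / 74.1 | 73.2 / 69.1 | 5.2, 5.0 |
| 0.9 | 34 | 86.3 / 83.3 | 82.0 / 79.2 | 4.3, 4.1 |

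With unequal classes, a separate simulation of 2,000 samples per setting gave an overstatement of J of 0.070 to 0.100 for 67 persistent and 33 resolved hips, and 0.083 to 0.113 for 53 and 27. At 67 per class the overstatement of J is 0.055 to 0.078.

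**3. How regular it is.** With 34 to 67 hips per class, the apparent sum of sensitivity and specificity exceeded the true sum in 82% to 90% of samples. Each measure alone was too high in 73% to 79%, and both together in 54% to 61%.

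**4. Other selection rules.** If the cut-off is set to give an apparent sensitivity of about 90%, the bias is +1.3 to +2.6 points in sensitivity and about 0 in specificity.

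**5. What the remedies achieve.** A cut-off fixed in advance showed bias between −0.4 and +0.2 points, which is zero within simulation error. Bootstrap optimism correction of the Youden cut-off left about +0.6 to +2.4 points (300 samples per setting, 60 resamples each).

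**6. Against sampling error.** For a true sensitivity of 73% and 67 hips, the 95% half-width is 1.96 × √(0.73 × 0.27/67) = 10.6 points. The bias is smaller than this, but it runs in one direction on average, and an interval computed as if the cut-off were fixed does not allow for it.

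**7. Stability of the cut-off.** Between samples of 67 per class it varied with an SD of 0.26 to 0.37 within-class SDs, and with 34 per class 0.32 to 0.43. A confidence interval for the cut-off is therefore informative.

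**The case against.** The strongest reply is that this is detail that a journal article leaves to the full protocol or SAP. The article gives the ROC analysis one sentence and excludes neither internal validation nor a confidence interval. That stands as a limit: one cannot say that validation will not be done. But the article does describe a chain in which a new value is derived, scored in the same data, and permitted to displace the old one in two later studies. Following that text as written gives optimistic accuracy.

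Four stronger readings are tempting, and the document does not support them.

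- A reader might infer that both measures are certain to be too high. The bias is an average, and it depends on a selection rule and class sizes that are not stated.
- A reader might infer that the cut-off triggers surgery throughout. That fits part 3 only. In part 2 it is an eligibility threshold for both arms, surgery is assigned by randomisation (section 2.2.2.2), and that comparison is not biased by optimism in the reported accuracy.
- A reader might infer that the plan abandons validation of 32.2%. Sections 2.2.2.1.1 and 2.2.3.2 keep 32% as the stated value with the new one as an alternative, and nothing prevents scoring 32.2% in part 1. Nor does the Abstract single out the cut-off as what awaits verification. It names the long-term fate of RLI and its correlation with RAD.
- A reader might infer that a single value should serve both later parts. The ROC predictor is initial inversion, measured on arthrography at reduction (section 2.2.1.3), while part 2 applies its threshold to inversion at follow-up. The document gives no basis for treating these as interchangeable.

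It is also fair to say that optimism in the accuracy does not show that a new cut-off would be a worse threshold than the one from the earlier small cohort.

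**Conclusion.** The point holds in a limited form. As described, part 1 reports accuracy for a data-chosen cut-off in the data that chose it, and that accuracy will be too high on average. Under a Youden rule and AUC 0.7 to 0.9, the overstatement is about 3 to 4 points in each of sensitivity and specificity with 67 hips per class, and about 4 to 6 points with 34. AUC, class sizes, the normal model and the selection rule are all assumptions, and other rules can give less.

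The consequence is an over-favourable description of how well the cut-off identifies hips with persistent RLI. No figure in the document changes. A separate but linked gap is that sections 2.2.2.1.1 and 2.2.3.2 each offer two thresholds without saying which one governs. The change is worth making because it is cheap and uses data already planned.

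**What to change.** 1. In section 2.2.1.4, item 3, report sensitivity and specificity with 95% confidence intervals for the prespecified 32.2% value in the part 1 cohort, leaving out any children who were in the earlier derivation cohort.
2. For any newly derived cut-off, state the selection rule, report bootstrap optimism-corrected or leave-one-centre-out accuracy, and give a confidence interval for the cut-off.
3. Before enrolment in parts 2 and 3, state which of the two values applies in each, and reconcile sections 2.2.1.4, 2.2.2.1.1 and 2.2.3.2 accordingly. Which threshold is clinically right is for the investigators, and none is proposed here.

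The cost is a little more analysis on the same data, and accuracy figures that will look slightly less favourable. Bootstrap correction may leave a small residual optimism, so the results for the fixed 32.2% value should be shown beside it.

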##### Inclusion criteria

2.2.1.1.

1.Pediatric patients undergoing closed reduction at 6–18 months of age;2.No other treatment prior to DDH reduction, with or without the administration of pre-reduction traction or percutaneous adductor tenotomy;3.After DDH reduction, a Spica cast was applied to immobilize the hips in ≤65° of abduction for 3 months, followed by use of abduction braces for 3 months;4.Patients must have a successful closed reduction, defined as a stable reduction enabling femoral head-acetabulum concentricity as suggested by frontal pelvic radiographs taken at 9–12 months after DDH reduction;5.Follow-up for more than 5 years.

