#### Primary outcome measures

2.3.1.

1.The improvement of the acetabular index2.Severin classification3.The magnitude of limbus inversion4.Avascular necrosis (AVN) of the femoral head was assessed based on the Kalamchi–MacEwen criteria.

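### The 67 per group and 90% power are computed from the final acetabular index, while the outcome named is its improvement, so the power for improvement is unknown

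*Protocol article*

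**What the plan says.** Section 2.2.1.4, item 4, sizes the retrospective cohort. It chooses the endpoint with the words "improvement of the acetabular index was the most suitable observation indicator". The next sentence gives the source of the inputs: "The sample size calculation was based on the previously published acetabular index at the final follow-up", with values "21.41°±3.61° and 18.88 ° ± 4.32° in the two groups, respectively" for the groups with and without residual limbus inversion. Significance level, power, allocation ratio and loss are fixed as follows: "the percentage of patients lost to follow-up were set at 0.05, 0.9, 1:1, and 20%, respectively". The result is 67 per group, 134 in all.

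Section 2.3.1 lists four primary outcomes, the first being "The improvement of the acetabular index". The analysis text in item 2 of section 2.2.1.4 begins "Differences in acetabular index was compared using" and names Student's t-test; it does not say whether the final value or the change enters the test. The same sentence recurs in sections 2.2.2.6 and 2.2.3.4. The article gives no index at reduction, mean change, SD of change or correlation between the index at reduction and at final follow-up.

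**The concern.** In ordinary usage, improvement is a change from a starting value. A change has a different SD from a final value, depending on how strongly the two measurements correlate. Here it may also have a different mean difference. The groups in section 2.2.1.4 are formed by limbus status, not by randomisation, so they may start from different index values. The Introduction itself names the acetabular index at reduction as a commonly used predictor of residual dysplasia.

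Two things are at stake. First, the quoted 90% may not describe the outcome to which the paragraph attaches it. Second, with the tested quantity left open, a t-test on final values would count any difference already present at reduction as an effect of the residual limbus, while a t-test on change would not.

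**Working it through.** **Reproducing the plan's figure**

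- Difference (section 2.2.1.4): 21.41 − 18.88 = 2.53°.
- Pooled SD: √[(3.61² + 4.32²)/2] = √15.85 = 3.98°. Standardised difference: 2.53/3.98 = 0.636.
- Two-sided 5%, 90% power: n = 2 × (1.960 + 1.282)² × 15.85 / 2.53² = 52.03, rounded up to 53 per group.
- Allowing for 20% loss: 53/0.8 = 66.25, rounded up to 67. This matches the article.
- The article does not state sidedness. A one-sided calculation gives 43, or 54 after inflation, so two-sided is inferred.
- Check with the noncentral t: power is 90.0% at 53 per group and 95.5% at 67.

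The published number is thus the size for a comparison of final values.

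**Power for a change score with the same numbers**

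The article does not give the necessary inputs. Assumptions: the same SD at reduction and at final follow-up, equal mean index at reduction (so the difference in change is 2.53°), and correlation r. Then SD of change = 3.98 × √[2(1 − r)].

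| r | SD of change | Power at 53 | Power at 67 |
|---|---|---|---|
| 0.2 | 5.04° | 73% | 82% |
| 0.3 | 4.71° | 78% | 87% |
| 0.4 | 4.36° | 84% | 92% |
| 0.5 | 3.98° | 90% | 95% |
| 0.6 | 3.56° | 95% | 98% |

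Under these assumptions 90% is reached at r = 0.50 with 53 evaluable per group and at about r = 0.37 with 67.

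**Unequal starting values**

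Suppose, as an illustration, that 1° of the 2.53° was already present at reduction. The difference in change is then 2.53 − 1 = 1.53°, and at r = 0.5 power is 50% at 53 and 60% at 67. If instead the group with residual inversion started 1° lower, the difference in change is 2.53 + 1 = 3.53°, and power is 95% at 53 even at r = 0.2.

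**Final value adjusted for the index at reduction (ANCOVA)**

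Residual SD = 3.98 × √(1 − r²). For a 2.53° adjusted difference, power at 53 is 91.1%, 92.5%, 94.3% and 96.3% for r = 0.2, 0.3, 0.4 and 0.5.

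With the same 1° gap at reduction and r = 0.5, the expected adjusted difference is 2.53 − 0.5 × 1 = 2.03° and the residual SD is 3.45°. Power is then about 85% at 53 and 92% at 67, ignoring a small loss from the association between group and starting value.

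**The case against.** The strongest defence is that improvement is loose wording. The article nowhere defines it as final minus initial value, and a two-sample t-test on the index is exactly what the calculation assumes, so sizing and test can be read as consistent. That reading is possible, but the text does not establish it: the word stands both in the sizing paragraph and in the primary outcome list, and the test sentence names no quantity. The ambiguity itself stands.

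A reader might go further and infer that the study is underpowered, or that 90% holds only if the correlation is at least 0.5 and the groups start equal. The documents support neither inference:

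- With 67 evaluable, about 0.37 suffices under the same assumptions. That case is credible for this cohort, because "Follow-up for more than 5 years" is an inclusion criterion and incomplete imaging an exclusion, so many losses fall before inclusion.
- A smaller spread at reduction also helps. An assumed baseline SD of 3.0° gives 91% at r = 0.4 with 53.
- A residual-inversion group that started lower, or a correlation above 0.5 with equal starting values, takes power above 90%.

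Two further objections bear on the remedy. Adjusted final values and change scores answer different questions when groups are not randomised, so adopting one is a choice to be stated, not a mere rewording. And the cohort follow-up list in section 2.2.1.3 ties only the initial limbus inversion expressly to the time of reduction; it does not say that the acetabular index was measured then. Both stand as limits. An outcome called improvement, however, needs the index at reduction in any case.

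**Conclusion.** The mismatch is certain: the endpoint named is improvement, the endpoint sized is the final value, and the test sentence does not settle which is compared. The arithmetic behind 67 is correct, and its 90% belongs to an unadjusted final-value comparison.

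The size and direction of the error for improvement are unknown. With equal SDs and equal starting values, power runs from 73% to 95% at 53 per group, and from 82% to 98% at 67, for r between 0.2 and 0.6. A 1° difference at reduction moves it substantially either way. Every correlation, the equality of SDs and the 1° gap are assumptions, not figures from the article. The point concerns the one of four primary outcomes to which the sample size is tied. It warrants correction but does not show that more patients are needed.

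**What to change.** In section 2.2.1.4, replace the t-test on an unspecified quantity with a primary analysis of the final acetabular index adjusted for the index at reduction (ANCOVA). Word the first primary outcome in section 2.3.1 to match. State that 67 per group and 90% power refer to a 2.53° baseline-adjusted difference. Outcome, test and sizing then describe the same quantity, and measured differences in starting index are taken into account. No common follow-up time is needed; age or time at final follow-up can enter as a covariate.

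The target of 67 can stay. There are two costs. Children without an index at reduction cannot contribute to this analysis, so its availability should be confirmed at each centre. And if part of the published 2.53° predates reduction, the stated power becomes less favourable: about 85% at 53 and 92% at 67 in the 1° illustration at r = 0.5. If the earlier cohort's index at reduction is available to the investigators, they should use it to replace these assumptions.
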